### Representativeness and Subgroup Considerations

Given that grant-stage external review previously highlighted the importance of rural-urban variation, recruitment records will capture each participant’s residence type (urban, peri-urban, or rural, based on the Census of India classification) and school type (government, government-aided, or private, where applicable) at both sites. Sample composition by residence type and school type will be reported descriptively and used, where numbers permit, as covariates in the multivariate regression models described below, to allow exploration of whether uptake and continuation differ between urban and rural or peri-urban participants. Given the feasibility-study sample size, these subgroup analyses will be considered hypothesis-generating rather than confirmatory.

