For the adolescent cohort, assuming a baseline sustainable-product usage rate of 5% and a projected postintervention uptake of 20%, with 80% power and 5% significance, the minimum required sample size was calculated as 304 adolescent girls per site using a standard formula for comparing 2-proportions formula. To account for clustering by school and community catchment, a design effect of 1.5 (based on an assumed intracluster correlation coefficient of 0.02 and an average cluster size of 25 girls, consistent with design effects reported in comparable school-based menstrual health cluster studies) was applied, giving a minimum requirement of 456 adolescent girls per site (total N=912) for the phase 2 sensitization cohort. Of these, a subgroup of 416 girls (n=208 per site) will be enrolled in the phase 3 product-use follow-up; this subgroup size was determined pragmatically in line with recommendations for feasibility and pilot studies, which emphasize that a fully powered comparative sample is not required at this stage but that sample size should still be justified in relation to the primary feasibility objectives (recruitment, retention, and product continuation) rather than a hypothesis-testing end point [22,23]. A minimum of 30‐35 participants per arm per site is considered adequate to estimate continuation and acceptability proportions with reasonable precision (95% CI width ≤±16%) for feasibility purposes, and the planned 203 girls per site substantially exceeds this threshold, allowing additional precision for the secondary comparison between MC and MP users. Twenty community health and education workers per site will be enrolled (total n=40) for training and postintervention assessment; this number reflects the total eligible cadre of ASHAs, ANMs, AWWs, and grade 8‐12 female teachers attached to the selected clusters at each site, and was not derived from a formal power calculation, consistent with standard practice for facilitator and trainer cohorts in implementation feasibility studies.

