### Phase 3: Intervention and Follow-up

A total of 416 adolescent girls aged 13‐19 years, equally divided between the 2 study sites, who complete the phase 2 sensitization and provide consent or assent for product use, will be allocated to either of the following:

MC group: receives a size-appropriate medical-grade silicone MC with instructional manual.MP group: receives 3 reusable MPs with instructional pamphlets.

Allocation to the MC or MP group will be based on participant preference following a structured counselling session in which both products, their insertion or use requirements, and maintenance needs are explained; girls who express no strong preference will be allocated using a randomization sequence generated in blocks of 4, stratified by site, to achieve approximately equal group sizes. This preference-informed allocation approach was chosen, rather than full randomization, because acceptability and correct use of MCs in particular are strongly influenced by willingness to use an internally inserted product, and forcing product allocation against strong preference was judged likely to compromise both retention and the validity of acceptability outcomes in a feasibility study of this nature; this deviation from a purely randomized design, and its rationale, is reported here transparently as recommended for feasibility study reporting [20].

Participants will receive free products along with instructional materials and menstrual-tracking diaries that record menstruation dates, school attendance, side effects, and usage challenges. Monthly follow-ups will occur through home visits at 1, 2, 3, 6, 9, and 12 months, conducted by trained community health and education workers using a structured follow-up checklist.

A 12-month follow-up duration was chosen in line with prior longitudinal descriptive work showing that adaptability and correct use of MCs typically stabilize only after several menstrual cycles of sustained use and support [25].

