Primary outcomes are product usage, continuation (proportion still using the allocated product at 12 mo), comfort, and acceptability (assessed using a structured acceptability scale administered at 1, 3, 6, and 12 mo, capturing ease of insertion or removal, comfort during daily activities, leakage experience, and overall satisfaction). Secondary outcomes include school absenteeism during menstruation, menstruation-related health complaints, and likelihood of recommending the product to others. FGDs conducted at 6 and 12 months will further explore facilitators and barriers to continued use.

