### Data Analysis

Quantitative data will be analyzed using SPSS (v25). Descriptive statistics (frequencies, means, and SDs) will be used to summarize participant characteristics and uptake. Paired 2-tailed *t* tests and chi-square tests will evaluate pre- and postintervention differences in knowledge, attitude, and practice scores. Multivariate logistic regression will examine predictors of product adoption and continuation, including site, residence type (urban or rural), age, product type (MC vs MP), and baseline knowledge and attitude scores, with statistical significance set at *P*<.05. Qualitative data will be analyzed thematically using NVivo (v14), following the 6-phase reflexive thematic analysis approach described above.

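### The only analysis named for the exploratory urban–rural question lists knowledge, attitude and product type alongside residence; entered together, they make the residence coefficient a conditional association, not the urban–rural difference in continuation

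*Protocol article*

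**What the plan says.** Representativeness and Subgroup Considerations says that residence type and school type will be "used, where numbers permit, as covariates in the multivariate regression models described below", and gives the purpose as "to allow exploration of whether uptake and continuation differ between urban and rural or peri-urban participants". The same section labels these analyses hypothesis-generating. The descriptive reporting it promises by residence is of sample composition.

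Data Analysis then describes the logistic regression for both outcomes and lists its predictors as follows: "including site, residence type (urban or rural), age, product type (MC vs MP), and baseline knowledge and attitude scores". The significance threshold is 0.05. The t tests and chi-square tests in that section are for pre-post differences in scores.

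Product type is mainly the girl's own choice: "Allocation to the MC or MP group will be based on participant preference following a structured counselling session". The exception is that "girls who express no strong preference will be allocated using a randomization sequence generated in blocks of 4, stratified by site". The share of girls in that exception is not stated.

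No analysis named in the article gives continuation by residence without the other predictors.

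**The concern.** Whether continuation differs between urban and rural girls is most naturally read as a question about the overall difference between two groups. A residence coefficient adjusted for knowledge, attitude and product answers another question: whether girls alike on those three still differ by residence.

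The two answers separate when the adjustment variables are themselves affected by residence, which is plausible here. The baseline scores precede the intervention, but they do not precede where a girl lives. The protocol's own COM-B framework treats knowledge and attitude as drivers of behaviour, so they are candidate routes from residence to continuation. Product follows counselling and preference, so for most girls it may also depend on the setting. Holding a chosen product fixed can in addition bring in bias from unmeasured reasons for the choice; I have not quantified that part.

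The comparison matters to this study. External review raised rural–urban variation, the northern catchment was extended to Panchkula to obtain it, and continuation is a primary outcome. A residence coefficient near 1 could be read as no difference between settings when fewer rural girls kept using the product, or the reverse. The same holds for the site coefficient.

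**Working it through.** The plan states no figure to reproduce, so the check is of what the coefficient measures. Every path strength below is assumed. The documents give no association of residence with knowledge, attitude or product choice. The sample size comes from the sample size section: "a subgroup of 416 girls (n=208 per site) will be enrolled in the phase 3 product-use follow-up" (the abstract gives 406). The regression is taken as two-sided at 0.05.

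**1. Product route alone, by hand.** Assume 60% of urban and 30% of rural girls have cups, and continuation is 60% with cups and 80% with panties in both settings.
- Urban: 0.6×0.6 + 0.4×0.8 = 0.68.
- Rural: 0.3×0.6 + 0.7×0.8 = 0.74.
- Urban-versus-rural OR: (0.68/0.32)/(0.74/0.26) = 2.125/2.846 = 0.75.
- OR adjusted for product: 1.0, because continuation within each product is the same in both settings.

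**2. Knowledge route alone.** Assume logit(continuation) = logit(0.7) + ln(1.5)×knowledge in SD units, with the rural mean 0.5 SD lower. Averaging over a normal distribution of knowledge gives:
- 69.3% urban against 65.0% rural, rural-versus-urban OR 0.82.
- OR adjusted for knowledge: 1.0 by construction.

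**3. Full covariate list, by simulation.** Assume 40% rural and 30% without a preference (randomised 1:1). Residence shifts knowledge, attitude and chosen product; unless stated, it has no other path to continuation. Model A has residence, site and age. Model B adds product, knowledge and attitude. ORs are rural versus urban, from n=400,000. The chance of P<.05 is from 800 runs at n=416.

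| Scenario | Urban / rural continuing | OR, A | OR, B | P<.05, A | P<.05, B |
|---|---|---|---|---|---|
| Weak paths | 74.3% / 69.9% | 0.81 | 1.00 | 17% | 4% |
| Moderate paths | 74.4% / 64.1% | 0.61 | 1.02 | 66% | 4% |
| Strong paths | 76.0% / 54.4% | 0.38 | 0.99 | about 100% | 4% |
| Knowledge and attitude only | 68.7% / 58.5% | 0.64 | 1.00 | 56% | 5% |
| Product only | 77.8% / 72.4% | 0.75 | 1.01 | 26% | 5% |
| Moderate paths plus an opposing direct path | 74.5% / 74.8% | 1.01 | 1.81 | 4% | 66% |

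For scale, the moderate row assumes rural knowledge and attitude 0.5 SD lower, log-odds of 0.5 per SD for each, cups chosen by 60% urban and 40% rural among girls with a preference, and log-odds of 0.6 for cups.

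**4. What the simpler model can show at n=416.** Assume two groups of 208, no attrition and no clustering. The half-width of the 95% CI for the risk difference is 1.96×√(p₁(1−p₁)/208 + p₂(1−p₂)/208).
- Step 1: SE 0.0444, half-width 8.7 points around a difference of 6 points; chance of P<.05 about 27%.
- Step 2: SE 0.0460, half-width 9.0 points around a difference of 4.3 points; chance of P<.05 about 16%.

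Unequal groups, attrition or clustering would widen these intervals.

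**The case against.** The strongest reply is that the regression is described as examining predictors, and in a predictor model a residence coefficient conditional on the rest is legitimate. Whether residence adds anything beyond knowledge and product is itself a fair exploratory question. The article never calls its target a total or causal difference, and residence comparison is not among the four specific objectives or the listed outcomes. This stands as a defence of keeping the model. It does not make the coefficient an answer to whether continuation differs between the settings, which is the purpose the article assigns to it.

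A second reply is that the text does not say how predictors are entered. It speaks of models in the plural and of using residence where numbers permit. An article may leave unadjusted or sequential results to the full protocol or analysis plan. This also stands: simultaneous entry is inferred from one condensed sentence, so the point is conditional on it.

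Third, girls with no strong preference are randomised, which weakens the product route. It does not touch the knowledge and attitude route, which alone gave an OR of 0.64 against 1.00 in the simulation.

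Fourth, the hypothesis-generating label limits how much weight the result can carry. That lowers the stakes, but it does not change what the coefficient measures.

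**Conclusion.** The point holds in a limited form. If the listed predictors are entered together, the only analysis named for the urban–rural question yields a conditional association that can miss a difference between settings or suggest one that is not there. The size is unknown. Across assumed scenarios without a direct path, gaps of about 4 to 22 percentage points appeared as adjusted ORs of 0.99 to 1.02; with an opposing direct path, near-equal continuation appeared as an OR of 1.81.

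A reader might infer more: that the plan will report a real rural gap as none, or that dropping the three predictors would turn a null result into a significant one. The documents support neither. They give no path strengths and no firm statement of simultaneous entry. For modest differences the simpler model would usually be non-significant too: about 27% and 16% chance of P<.05 in the two hand examples, and 17% in the weak-path simulation. Only the larger assumed gaps change that verdict markedly. What is gained is the right estimate and its interval, for an exploratory comparison in a feasibility study.

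**What to change.** - Report 12-month continuation by residence type, with a risk difference and 95% CI from a model containing residence and site only (optionally age), allowing for the school and catchment clusters. Name this as the exploratory answer to the question posed under Representativeness and Subgroup Considerations.
- Keep the regression under Data Analysis as a secondary predictor model, state how its predictors are entered, and add a sentence that its residence and site coefficients are conditional on knowledge, attitude and product and are not to be read as the difference between settings.
- Present the result as an estimate with its interval and not by whether it passes P<.05.

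The cost is one extra model on data already being collected and a sentence or two of text. Analysis is planned for the first quarter of 2027, so this can be settled before any outcome is analysed by residence.

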### Data Analysis

Quantitative data will be analyzed using SPSS (v25). Descriptive statistics (frequencies, means, and SDs) will be used to summarize participant characteristics and uptake. Paired 2-tailed *t* tests and chi-square tests will evaluate pre- and postintervention differences in knowledge, attitude, and practice scores. Multivariate logistic regression will examine predictors of product adoption and continuation, including site, residence type (urban or rural), age, product type (MC vs MP), and baseline knowledge and attitude scores, with statistical significance set at *P*<.05. Qualitative data will be analyzed thematically using NVivo (v14), following the 6-phase reflexive thematic analysis approach described above.

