#### Phase 1: Stakeholder Sensitization

##### Workshops

Workshops will be conducted with 40 community health and education workers to build knowledge of menstrual health, sustainable menstrual hygiene practices, MC and MP use, benefits, myths, and insertion and removal demonstrations, using the module described above. A toolkit including information, education, and communication materials, demonstration videos, and posters will be used across 2 half-day workshops per site; the workshops will be delivered by the study team. Pre-post assessments will evaluate changes in knowledge, attitude, and comfort with discussing the topic (see below). Trained community health and education workers will subsequently engage adolescent girls through interactive sessions in schools and community settings using the adolescent-facing module.

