### Phase 2: Adolescent Sensitization and Recruitment

The sensitization intervention will be conducted in small-group workshops (approximately 20‐25 girls per group) using materials developed and validated in phase 1, covering menstrual health, hygiene, and correct usage of MCs and MPs. Sessions will be led by previously trained community health and education workers (ASHA, ANM, AWW, and female teachers), ensuring cultural sensitivity and local relevance, and will run for approximately 90 minutes across 2 sessions per group. Adolescents will be recruited as per the inclusion criteria above through school registers (for school-going girls) and community health worker household lists (for out-of-school girls), with information sessions held for parents and guardians prior to enrollment. Preintervention and postintervention questionnaires (structured, self-administered, in the local language) will measure changes in knowledge, attitudes, and perceived readiness to adopt MC and MP, using the same core knowledge and attitude domains as the phase 1 instrument, adapted to the adolescent literacy level. Additionally, 2 focus group discussions (FGDs) will be held at each site—one with adolescent girls and one with their female guardians—to explore barriers and facilitators to product adoption, using a semistructured topic guide based on the COM-B framework (Multimedia Appendix 2). Quantitative data will be analyzed using SPSS (version 26; IBM Corp), and qualitative data will undergo thematic analysis to develop a comprehensive understanding of the social and behavioral influences on sustainable menstrual product adoption.

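### Chi-square tests are named for before-after comparisons in the same people; categorical items need a paired test

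*Protocol article*

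**What the plan says.** The Data Analysis section of the protocol article gives one sentence to the before-after comparisons. It opens with "Paired 2-tailed *t* tests and chi-square tests", and on the second of these it reads: "chi-square tests will evaluate pre- and postintervention differences in knowledge, attitude, and practice scores". Significance is declared "with statistical significance set at *P*<.05".

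The comparisons are made within people. For the 40 workers, the Workshops section says: "Pre-post assessments will evaluate changes in knowledge, attitude, and comfort with discussing the topic". For the girls, the Phase 2 section says: "Preintervention and postintervention questionnaires (structured, self-administered, in the local language) will measure changes in knowledge, attitudes, and perceived readiness to adopt MC and MP". Neither phase has a control group for these outcomes.

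No paired categorical test is named anywhere in the article. The logistic regression in the same section concerns predictors of adoption and continuation, not change from before to after.

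**The concern.** The paired t test shows that the authors regard the data as paired. The test named beside it for categorical results does not use the pairing, and it can be run in two ways:

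- **Time by response.** Each person enters the table twice, as if two different people had answered. The standard error leaves out the within-person covariance, so with positive correlation it is too large.
- **Before-answer by after-answer.** Each person enters once, but the test then asks whether the two answers are associated, not whether the proportion changed.

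At stake are the P values for every categorical item or categorised score in the first two objectives. The number of workers is fixed at 40, so power lost there through the choice of test cannot be regained by recruiting more.

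**Working it through.** **Inputs from the article.** 40 workers; 912 girls, 456 per site; significance level 0.05; design proportions 5% before and 20% after.

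**Assumed, because the article does not give them.** The within-person correlation phi, shown as a range, and the illustrative changes 50% to 70% (n=40) and 50% to 55% (n=912). Tests are two-sided.

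**The plan's own figure.** The only computed figure nearby is 304 girls per site for 5% versus 20% at 80% power. The usual two-sided formula gives [1.96 × √(2 × 0.125 × 0.875) + 0.842 × √(0.05 × 0.95 + 0.20 × 0.80)]² / 0.15² = 1.300² / 0.0225 = 75.1, so 76 per group. The 304 is not reproduced (it equals 4 × 76). That is a separate matter, and nothing below depends on it.

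**Step 1: standard error.** With proportions p1 and p2 in the same n people, the variance of the difference is [p1(1−p1) + p2(1−p2) − 2·phi·√(p1(1−p1)p2(1−p2))] / n. The ordinary chi-square test omits the last term. With no change and p = 0.5, the true variance is 0.5(1−phi)/n, while chi-square uses 0.5/n. At n=40 and phi 0.4 the true standard error is √(0.3/40) = 0.087, against 0.112 used.

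**Step 2: type I error.** The effective critical value is 1.96/√(1−phi), that is 2.19, 2.53 and 3.10 at phi 0.2, 0.4 and 0.6. The large-sample error rates are then 2.8%, 1.1% and 0.2%. Simulation at n=40 gives slightly higher values because the counts are discrete (table below).

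**Step 3: power at n=40, 50% to 70%.** The share correct both times is 0.35 + phi × √(0.25 × 0.21) = 0.35 + 0.229·phi. At phi 0.4 that is 0.442, so 5.8% go from right to wrong and 25.8% from wrong to right. Simulated results:

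| phi | chi-square, type I error | chi-square, power | McNemar asymptotic, power | McNemar exact, power |
|---|---|---|---|---|
| 0 | 5.7% | 46% | 45% | 36% |
| 0.2 | 3.2% | 45% | 52% | 43% |
| 0.4 | 1.4% | 44% | 63% | 54% |
| 0.6 | 0.3% | 42% | 86% | 75% |

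The largest phi these margins allow is 0.15/0.229 = 0.65, so the last row lies near the ceiling.

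**Step 4: power at n=912.** For 50% to 55%, chi-square has 59% and asymptotic McNemar 72% at phi 0.3; at phi 0.5 the figures are 61% and 85%. For 5% to 20%, both have power of about 1.00 at n=456 and at n=912, at phi 0 and 0.3.

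**Step 5: the pre-by-post table.** Two constructed examples with 40 people:

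- 18 right both times, 18 wrong both times, 2 changing each way. Exactly half are right before and after. Pearson's test gives P = 4 × 10⁻⁷; McNemar's gives P = 1.0.
- 4 right both times, 7 wrong both times, 28 changing to right, 1 to wrong. Correct answers rise from 5/40 to 32/40. Pearson's test gives P = 1.0; McNemar's statistic is (28−1)²/29 = 25.1, P = 5 × 10⁻⁷.

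**The case against.** **The wording may be loose naming.** McNemar's test is itself a chi-square-type test, and the word paired could be stretched over both tests in the sentence. That lowers certainty about what the authors intend. It does not settle the text: paired and 2-tailed belong naturally to the t tests, and a reader who follows the sentence as written would run the ordinary test. Nor is this a detail left to a fuller document, since the article does name a test.

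**The loss can be small or absent.** This stands in part. At phi 0 nothing is lost. At phi 0.2 the exact McNemar test has slightly less power than chi-square (43% against 45%), although chi-square then runs at 3.2% instead of 5%. The gain is clear only at moderate or high phi, or for modest changes in a large sample.

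**Objective 1 may seem to rest on this test.** A reader might infer that, but the article does not support it. Table 1 and the Results section describe knowledge and attitude scores, and an increase in mean knowledge scores; these go to the paired t test, which is correct. No binary phase 1 endpoint is named, and the 40 workers were not set by a power calculation.

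**The direction is mostly harmless.** In the time-by-response form the error from ignoring pairing is conservative, so a reader should not infer false claims of benefit from it. That reassurance does not cover the pre-by-post form, which can be significant when nothing has changed.

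**Conclusion.** The point holds for categorical items and categorised scores. As written, the plan names a test that does not fit before-after data on the same people: in one form it is miscalibrated, in the other it answers a different question.

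The size depends on an assumed phi. In the n=40 example, chi-square compares with the asymptotic McNemar test anywhere from no loss at phi 0 to about 19 points at phi 0.4 (44% against 63%), and more near the upper limit of phi. At n=912 and phi 0.3 the loss is about 13 points for a 5-point change.

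Three wider inferences are not supported. The phase 2 design contrast of 5% to 20% is not endangered, since power is about 1.00 either way. The analysis of mean scores is not affected. And it cannot be said that reported intervals will be too wide, because the Data Analysis section plans no interval for these differences. This is a clear error with modest consequences, worth correcting before the analysis planned for early 2027.

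**What to change.** State in Data Analysis that categorical before-after comparisons use McNemar's test for binary items and a marginal homogeneity test for ordinal or multi-category items, on records linked by participant ID, with the paired difference in proportions and its 95% CI. For the 40 workers, say whether the exact or the asymptotic McNemar test applies. Reserve the ordinary chi-square test for independent groups, such as site against site or cup users against panty users.

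The cost is one or two sentences. The tests are available in SPSS, and the ID linkage is already required by the paired t test. A GEE or mixed logistic model for phase 2 would also carry the school and catchment clustering that the Study Setting and Sample Size sections acknowledge. It is optional and is not needed to correct the pairing.

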### Study Setting and Rationale for Site Selection

The study will take place in 2 Indian sites, chosen to capture contrasting geographic and sociocultural contexts while retaining the feasibility of implementation within the study team’s existing institutional and field infrastructure (Figure 1):

Center 1—East India (Kalyani, West Bengal): Kalyani is a planned urban township in the Nadia district of West Bengal, approximately 50 kilometers (31 miles) from Kolkata. It functions as both a municipality and a community development block, and includes surrounding semiurban and rural catchment areas served by the affiliated primary health centers, allowing the capture of both urban and semirural adolescent populations within a single site.Center 2—North India (Chandigarh and Panchkula): Chandigarh is a union territory serving as the joint capital of Haryana and Punjab, recognized for its planned urban infrastructure. The study will include defined urban service areas of Chandigarh (Indira Colony and Sectors 25, 49, 50, and 52), together with Panchkula district, Haryana, which includes peri-urban and rural blocks, to allow comparison of urban and rural uptake within the same site.

The 2 sites were selected, in preference to a larger number of sites, to allow intensive, high-fidelity delivery of the facilitator-training and adolescent-sensitization components within the resources available for a feasibility study, while still enabling comparison across an eastern, planned-urban context (Kalyani) and a northern, mixed urban-rural context (Chandigarh-Panchkula). Recruitment at each site is organized at the level of predefined clusters (schools and their linked Anganwadi and health subcenter catchments), reflecting the fact that stakeholders and adolescent girls are naturally grouped within schools and community health worker catchment areas rather than sampled as unrelated individuals; this clustering was accounted for in the sample size calculation (see below) via a design effect. This represents a refinement of the original grant proposal, in which site selection was described in less detail; following external review of the funded proposal, the protocol was revised to make the cluster structure explicit and to ensure that both urban and rural and peri-urban catchments are represented at each site, rather than urban areas only, in order to improve generalizability of findings across the rural-urban gradient.

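### The sample size is inflated for clustering by school and catchment, but the named analyses carry no cluster term, so precision is overstated for between-cluster contrasts and overall proportions

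*Protocol article*

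**What the plan says.** The protocol article describes a clustered design. Under Study Setting and Rationale for Site Selection: "Recruitment at each site is organized at the level of predefined clusters (schools and their linked Anganwadi and health subcenter catchments"). The same paragraph says where this is dealt with: "this clustering was accounted for in the sample size calculation (see below) via a design effect".

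Study Flow and Sample Size Calculation gives the inputs: "a design effect of 1.5 (based on an assumed intracluster correlation coefficient of 0.02 and an average cluster size of 25 girls"). It starts from 304 girls per site and arrives at 456: "giving a minimum requirement of 456 adolescent girls per site (total N=912").

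The Data Analysis section names the analyses. Pre-post differences in knowledge, attitude and practice are tested with two-tailed paired t tests and chi-square tests. Adoption and continuation are modelled as follows: "Multivariate logistic regression will examine predictors of product adoption and continuation, including site, residence type (urban or rural), age, product type (MC vs MP"), with baseline knowledge and attitude scores also in the model and significance set at P<.05. Representativeness and Subgroup Considerations adds residence type and school type as covariates where numbers permit. No section mentions a random effect, GEE, a cluster-robust variance or a design-effect correction in the analysis.

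**The concern.** Paired t tests and chi-square tests as named treat girls as independent, and so does logistic regression unless something is added to it. Girls from the same school or catchment share a setting, facilitators and workshop sessions, and the plan itself assumes that their outcomes correlate. The covariates do not stand in for the clusters: site has two levels, and residence and school type are broad categories.

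Standard errors are therefore too small for quantities that depend on variation between clusters: the site comparison, residence and school type as far as these differ between rather than within clusters, and overall proportions such as uptake and continuation. Intervals for these would be too narrow, and the 5% level would not hold. Between-site and urban-rural differences are the results most exposed to overstatement.

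**Working it through.** **Inputs.** Intracluster correlation (ICC) 0.02, average cluster size m = 25, design effect 1.5, 304 and 456 girls per site, 912 in total, and a phase 3 subgroup of 416 (all from Study Flow and Sample Size Calculation). The 304 is taken as stated; this point does not depend on it.

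**1. The plan's own figure.** Design effect = 1 + (m − 1) × ICC = 1 + 24 × 0.02 = 1.48, rounded in the plan to 1.5. Then 304 × 1.5 = 456 per site, and 2 × 456 = 912. The figures reproduce.

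**2. Effect of leaving clustering out, phase 2 cohort.** For a between-cluster contrast or an overall proportion:
- The correct standard error is √1.48 = 1.22 times the naive one; equivalently the naive one is 1/1.22 = 0.82 of the correct one, about 18% too small.
- True size of a nominal 5% test = 2 × [1 − Φ(1.96/√1.48)] = 2 × [1 − Φ(1.61)] ≈ 10.7%.
- Coverage of a nominal 95% interval ≈ 89.3%.
- Effective sample size = 912/1.48 ≈ 616.

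**3. Phase 3.** The article gives no phase 3 cluster size. Assumption: the 416 girls are spread over the same clusters in proportion, so m = 25 × 416/912 ≈ 11.4.
- Design effect = 1 + 10.4 × 0.02 ≈ 1.21, and √1.21 = 1.10.
- True size ≈ 7.5%, coverage ≈ 92.5%, effective sample size ≈ 416/1.208 ≈ 344.
- The abstract's figure of 406 gives m ≈ 11.1 and a size of about 7.4%, so the choice does not matter here.

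**4. Sensitivity to the ICC (assumed values).**

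| ICC | Size, m = 25 | Size, m = 11.4 |
|---|---|---|
| 0.01 | 7.8% | 6.2% |
| 0.02 (plan) | 10.7% | 7.5% |
| 0.05 | 18.6% | 11.2% |

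**5. Simulation check.** Plain logistic regression was run with beta-binomial outcomes, 36 clusters (912/25 ≈ 36), two null covariates and 1,500 replicates per setting. The outcome rate was 20% with 25 girls per cluster and 70% with 11.

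| Setting | Cluster-level covariate | Individual-level covariate |
|---|---|---|
| 25 per cluster, ICC 0.02 | 11.4% | 4.8% |
| 25 per cluster, ICC 0.05 | 18.3% | 5.9% |
| 11 per cluster, ICC 0.02 | 8.2% | 5.2% |

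The inflation sits with the cluster-level covariate. Uncorrected cluster-robust standard errors brought its rejection rate back to about 6–7% in each setting. That is close to nominal but still slightly high, which is why a small-sample correction is advisable.

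**6. Pre-post comparison.** Take the plan's planning rates, 5% and 20%, with 456 girls per site, and treat the two occasions as independent. The naive standard error is √[(0.05 × 0.95 + 0.20 × 0.80)/456] = 0.0213, so z = 0.15/0.0213 ≈ 7.0. Even with the full design effect, z = 7.0/1.22 ≈ 5.8. Significance would not be lost. Stable differences between clusters cancel in within-girl change, so the ICC of 0.02 need not carry over to change scores.

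**The case against.** The strongest reply has four parts.

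- **The article is a summary.** Its regression wording does not exclude robust, GEE or random-effects estimation, and variance estimation is often left to a fuller document. For the regression alone this has some force. It does not dispose of the point: the section fixes the tests, the covariates, the significance level and the software, the t and chi-square tests as named have no place for a cluster, and the article says that clustering was handled in the sample size.
- **Much of the analysis is not affected.** This stands. Age and baseline scores vary mainly within clusters. Product type follows individual preference, or blocked randomization where a girl has no strong preference, so it is affected only if choice of product clusters by school. Residence type is recorded per girl and both sites mix settings, so how far it varies between clusters is not documented.
- **The distortion is moderate and smaller in phase 3**, and a large pre-post shift would survive it. This also stands.
- **This is a feasibility study.** Phase 3 is not sized for hypothesis testing, and the residence and school-type analyses are declared exploratory. This lowers the severity, but it does not cover the site effect, the pre-post tests or the intervals around reported proportions.

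A reader might infer something worse from the statement that the 20 workers per site are the whole eligible cadre. If every cluster needed its own worker from each of the four cadres, there could be at most 5 clusters per site of about 91 girls, a design effect of 2.8 and a size of about 24%. The article nowhere says that clusters are staffed this way or that workers are not shared, and the scenario conflicts with its stated average of 25 girls. That figure should not be used.

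**Conclusion.** The point holds with limited scope. The plan recognizes clustering in its sample size and then names analyses without a cluster term. Followed as written, this gives a true size of about 10.7% and coverage of about 89% for between-cluster contrasts and overall proportions in phase 2, and about 7.5% and 92.5% in phase 3. These figures rest on the plan's ICC of 0.02 and cluster size of 25 and, for phase 3, on an assumed 11.4 girls per cluster.

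A reader might conclude that every P value in the study is too small, or that the extra recruitment is wasted. Neither follows. Within-cluster predictors are essentially unaffected, the added girls still contribute information, and a rise from 5% to 20% would remain significant, though its interval may be too narrow to the extent that change scores cluster. For a feasibility study this should be fixed before analysis, but it does not threaten the main conclusions.

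**What to change.** Amend the Data Analysis section so that the school/catchment cluster defined under Study Setting is the unit of clustering:

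- **Pre-post scores in girls:** a mixed model with a cluster random effect on the change (change scores with a cluster intercept, or a cluster-by-time term). A cluster intercept on the level of the score alone would not capture clustering of change.
- **Adoption and continuation:** GEE or mixed logistic regression with cluster as the subject and a small-sample correction, since only about 36 clusters are implied.
- **Reported proportions:** cluster-robust confidence intervals.
- **Reporting:** the number and size of clusters in each phase, and the observed ICC for the main outcomes.

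SPSS, already the chosen software, offers these models through MIXED, GENLIN and GENLINMIXED. The cost is a change of analysis wording and retention of the cluster identifier. Clusters are predefined and analysis is planned for early 2027, so there is time. Under the plan's ICC, intervals for cluster-level contrasts and overall proportions become about 22% wider in phase 2 (√1.48 = 1.22) and about 10% wider in phase 3 (√1.21 = 1.10).
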